# Mechanochemical endovenous ablation versus radiofrequency ablation in the treatment of primary small saphenous vein insufficiency (MESSI trial): study protocol for a randomized controlled trial

**DOI:** 10.1186/1745-6215-15-421

**Published:** 2014-10-29

**Keywords:** Mechanochemical ablation, ClariVein, radiofrequency ablation, varicose vein, therapy, treatment, MOCA, outcome

## Abstract

**Background:**

Minimally invasive endothermal techniques, for example, radiofrequency ablation (RFA), have revolutionized the treatment of insufficient truncal veins and are associated with an excellent outcome. The use of thermal energy requires the instillation of tumescent anesthesia around the vein. Mechanochemical endovenous ablation (MOCA™) combines mechanical endothelial damage, using a rotating wire, with simultaneous infusion of a liquid sclerosans. Tumescent anesthesia is not required as no heat is used. Prospective studies using MOCA™ in both great and small saphenous veins showed good anatomical and clinical results with fast postoperative recovery.

**Methods/Design:**

The MESSI trial (Mechanochemical Endovenous ablation versus radiofrequency ablation in the treatment of primary Small Saphenous vein Insufficiency) is a multicenter randomized controlled trial in which a total of 160 patients will be randomized (1:1) to MOCA™ or RFA. Consecutive patients with primary small saphenous vein incompetence, who meet the eligibility criteria, will be invited to participate in this trial. The primary endpoint is anatomic success, defined as occlusion of the treated veins objectified with duplex ultrasonography at 1 year follow-up. Secondary endpoints are post-procedural pain, initial technical success, clinical success, complications and the duration of the procedure. Initial technical success is defined as the ability to position the device adequately, treat the veins as planned and occlude the treated vein directly after the procedure has been proven by duplex ultrasonography. Clinical success is defined as an objective improvement of clinical outcome after treatment, measured with the Venous Clinical Severity Score (VCSS). Power analyses are conducted for anatomical success and post-procedural pain.

Both groups will be evaluated on an intention-to-treat principle.

**Discussion:**

The hypothesis of the MESSI trial is that the anatomic success rate of MOCA™ is not inferior to RFA. The second hypothesis is that post-procedural pain is significantly less after MOCA compared to RFA.

**Trial registration:**

Trial registration: NTR4613 Date of trial registration: 28 May 2014.

## Background

Varicose veins are common and symptoms range from cosmetic complaints to venous ulcers. The incidence increases with age and women are more affected than men. The majority of venous associated complaints are due to great saphenous vein (GSV) insufficiency; however, in 15% of patients, small saphenous vein (SSV) insufficiency is the main cause [1–3].

During the last decade, minimally invasive endothermal catheter modalities took over the role of surgical therapy in the treatment of small saphenous insufficiency. Surgery has been associated with high recurrence rates (25 to 60%), nerve injuries, and significant postoperative complications [4–10]. Success rates after endothermal catheter techniques, for example, endovenous laser ablation (EVLA) and radiofrequency ablation (RFA), are excellent. At 1 year follow-up, the anatomical success rate of RFA is 88% [10]. RFA is associated with fewer procedure-related symptoms, superior cosmetic results and earlier resumptions of daily activity compared to traditional surgical procedures [11, 12]. However, to perform endothermal techniques, tumescent anesthesia is essential. Furthermore, heat-induced nerve injury and post-procedural pain is inherent to endothermal ablation and can become chronic. Nerve injuries after endothermal ablation of SSV are seen in up to 11% [13].

Mechanochemical endovenous ablation (MOCA™), using the ClariVein™ system (Vascular Insights LLC, Madison, CT, USA) was introduced in Europe in 2010. Mechanical injury to the endothelium by a rotating wire at the tip of a catheter is combined with an infusion of liquid sclerosans, without the use of tumescent anesthesia. In Europe, the ClariVein™ device was registered on April 26, 2010, CE 558723.

Recently, the authors published the first results of MOCA™ in SSV. Occlusion rates in 50 patients were 100% at 6 weeks follow-up and up to 97% at 1 year. In this cohort of SSVs, no major complications, including nerve injury, were seen. Minor complications, such as localized ecchymoses and superficial thrombophlebitis were seen in 12 to 14%. The Venous Clinical Severity Score (VCSS), an objective measure for varicose vein-specific symptoms, improved significantly from 3 (IQR 2 to 5) before treatment to 1 (IQR 1 to 3, *P* <0.001) at 6 weeks follow-up. Clinical results were retained at 1 year after treatment (VCSS 1, IQR 1 to 2, *P* <0.001). Patients were satisfied after treatment [14]. Several other studies reported promising data on feasibility, safety, anatomical and clinical success regarding MOCA treatment in GSV insufficiency, without major complications [15–17].

## Method/Design

### Study design

The multicenter randomized clinical MESSI trial is designed to compare MOCA™ and RFA in the treatment of SSV insufficiency. Patients with primary SSV insufficiency, meeting eligibility criteria, will be included at the outpatient clinics of the participating hospitals after giving written informed consent. The procedures are performed or supervised by dedicated vascular surgeons, who have performed over 20 procedures of both treatment modalities.

The following Dutch vascular centers are participating in the MESSI trial: St. Antonius Hospital Nieuwegein, Rijnstate Hospital Arnhem and Rode Kruis Hospital Beverwijk.

### Study objectives

The aim of the study is to show that MOCA™ has no inferior anatomical success compared to RFA at 1 year follow-up. The secondary aim is to evaluate post-procedural pain, which is hypothesized to be significantly less after MOCA™.

### Sample size calculation

Power analysis is calculated for anatomical success at 1 year follow-up after endovenous treatment of the SSV. The calculation is based on the hypothesis that MOCA™ will have no inferior occlusion rates at 1 year after treatment compared to RFA. The meta-analysis by Van de Bos *et al*. showed anatomical success rates of 88% after RFA [10]. Our recent study on MOCA™ in SSV showed an occlusion rate of 97% in the group treated according to our current study protocol [17]. A Chi-square test with a one-sided 0.05 significance has a power of 80% to observe no difference between both groups, when each group consists of 74 patients (non-inferiority principle, range 2%). The study population of both groups will consist of 148 patients. Corrected for 7.5% lost to follow-up, the total study population will consist of 160 patients.

Pain is an important secondary outcome parameter. A sample size calculation is also performed for this endpoint based on the hypothesis that MOCA™ will have lower post-procedural pain scores, as measured by a 100-point pain score, during the first two weeks after surgery. To evaluate a 30 percent reduction in post-procedural pain, 58 patients per group are needed (alpha 5%, power 80%). This analysis will be performed after inclusion and randomization of at least 58 patients in each group.

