### Statistical analyses

The study results will be evaluated based on intention-to-treat analysis. Data concerning the 1, 2, and 5 years follow-up will be analyzed for both study groups on an intention-to-treat manner by student t-test (normal distribution) or Mann Whitney U-test (skewed distribution). To test for normality, the Kolmogorov-Smirnov test will be used. The Chi-square test will be used for binomial data. All probability values are two-tailed. *P* <0.05 will be considered significant. Obliteration rates will be presented as Kaplan Meier curves, including censoring in case of loss to follow-up.

An interim analysis will be performed after treatment and at 4 weeks follow-up for the first 80 patients to monitor the progression of the study. Final analysis will be performed after follow-up of the last patient included in this study is completed.

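### The primary non-inferiority test is sized at one-sided 0.05 but analysed under a rule that makes every test two-tailed at 0.05; under that rule power at 74 per arm is about 73%, not 80%

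*Protocol article*

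**What the plan says.** The protocol article fixes the error level of the primary comparison in two places.

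- **Sample size calculation.** The hypothesis is that occlusion at 1 year after MOCA is not inferior to RFA. The power statement reads "A Chi-square test with a one-sided 0.05 significance has a power of 80" per cent. The inputs are a meta-analysis that "showed anatomical success rates of 88% after RFA", a cohort that "showed an occlusion rate of 97% in the group treated according to our current study protocol", a non-inferiority range of 2% and 74 patients per group. The total of 148 is raised to 160 for 7.5% loss to follow-up.
- **Statistical analyses.** "The Chi-square test will be used for binomial data". The next sentence is "All probability values are two-tailed", and a P value "<0.05 will be considered significant". Occlusion at 1 year is a binomial outcome, so these sentences cover it. Nothing in the section treats the primary endpoint differently.

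**The concern.** A two-tailed test at 0.05 spends 0.025 in each direction. Non-inferiority is decided in one direction only, so the analysis rule implies one-sided 0.025, half the error that the sample size assumes. That matters in two ways.

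- If the analysis section governs, the trial does not have the power it states.
- If neither section clearly governs, the threshold for the primary claim is open. A result can pass at one-sided 0.05 and fail at one-sided 0.025, and the article would support either reading after the data are known.

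**Working it through.** **Inputs (Sample size calculation).** RFA 0.88; MOCA 0.97; margin 0.02, read as 2 percentage points; 74 per group; one-sided 0.05; power 80%; loss 7.5%. From Statistical analyses: two-tailed 0.05, so 0.025 in the direction of interest.

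**Formula.** Normal approximation with unpooled variance:

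power = Φ[(0.97 − 0.88 + 0.02) / SE − z]

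- Variance term: 0.88 × 0.12 + 0.97 × 0.03 = 0.1056 + 0.0291 = 0.1347.
- SE = √(0.1347 / 74) = 0.04266.
- Distance from the margin: 0.11 / 0.04266 = 2.578.

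**Step 1: the plan's own figure.** At one-sided 0.05, z = 1.645 and power = Φ(0.933) = 82.5%. With pooled variance under the null it is 81.8%. Both are close to the stated 80%. The same formula needs 0.1347 × (1.645 + 0.842)² / 0.11² = 68.8, so 69 per group (71 with pooled variance). The stated 74 is therefore slightly generous. The inflation for loss reproduces: 148 / 0.925 = 160.

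**Step 2: the analysis section's level.** At two-tailed 0.05, z = 1.960 and power = Φ(0.618) = 73.2% (72.2% pooled).

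**Step 3: size needed at that level.** 0.1347 × (1.960 + 0.842)² / 0.11² = 87.4, so 88 per group, or 176 evaluable. 176 / 0.925 = 190.3, so 191 randomised against 160 planned.

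**Step 4: sensitivity to the test and the numbers analysed.**

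| Method | One-sided 0.05 | Two-tailed 0.05 |
|---|---|---|
| Unpooled normal approximation, 74 per group | 82.5% | 73.2% |
| Pooled normal approximation, 74 per group | 81.8% | 72.2% |
| Score test, exact enumeration, 74 per group | 84% | 74% |
| Wald test, exact enumeration, 74 per group | 86.2% | 77.8% |
| Unpooled normal approximation, 80 per group (no loss) | 85.0% | 76.5% |

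Every entry in the right-hand column is below 80%, and the fall is about 8 to 10 points.

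**Step 5: a result that splits the two rules.** Take 70/74 occluded after MOCA and 65/74 after RFA. The difference is 5/74 = 6.76 points with a Wald SE of 4.62 points.

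- Lower limit of the 90% interval: 6.76 − 1.645 × 4.62 = −0.8 points, inside the 2-point margin.
- Lower limit of the 95% interval: 6.76 − 1.960 × 4.62 = −2.3 points, outside it.

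Under the protocol's assumed rates, the chance that the Wald test passes one rule and fails the other is 86.2% − 77.8% = 8.4%.

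**The case against.** The strongest reply is that the sample size section speaks specifically about the primary hypothesis, while the two-tailed sentence is general and was probably meant for the other endpoints. On that reading one-sided 0.05 governs and no power is lost. This may be what was intended, but the text does not say so. The general sentence covers all probability values, and the sentence just before it assigns the test for binomial outcomes, of which the primary endpoint is one.

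Three further points are fair and limit how the figures should be used.

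- **Baseline.** The 73% is a fall from 82.5%, because 74 per group exceeds what the formula needs. Starting from exactly 80%, the same change would end near 70%. Depending on method, the end point lies between about 70% and 78%.
- **The interval is inferred.** Neither section mentions a confidence interval. Read literally, the analysis section prescribes an ordinary two-tailed Chi-square test of difference, which does not test against a margin at all. The 73% assumes a non-inferiority test run at the stated two-tailed level.
- **A larger dependence.** All these powers assume that MOCA is truly 9 points better than RFA. If both rates were 88%, power with 74 per group would be about 10% at one-sided 0.05 and 6% at two-tailed 0.05.

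An unseen statistical analysis plan does not remove the problem. This is not a detail left out: two explicit statements conflict, and a plan could follow one only by departing from the other.

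**Conclusion.** The concern holds. The article sets two error levels for its primary hypothesis and does not say which applies. Under the analysis section's level, power at 74 per group is about 73%, compared with 82.5% by the same formula at the level used for sizing and 80% as stated. The power figures rest on the protocol's rates of 88% and 97%, on reading the 2% range as percentage points, and on a non-inferiority test against that margin. The contradiction depends on none of these. It must be fixed because it concerns the decision rule for the primary endpoint and can change the trial's conclusion.

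**What to change.** State one level for the primary test and use it in both sections. Either of the following would do.

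- **(a) Exempt the primary test.** Add to Statistical analyses: *the primary non-inferiority test is one-sided at 0.05, judged by the lower limit of the two-sided 90% confidence interval for the difference in occlusion; all other tests are two-tailed.* The sample size text then stands.
- **(b) Keep two-tailed 0.05.** State that non-inferiority is judged by the 95% confidence interval, change the level in the sample size section to match, and restate the power at 74 per group as about 73% at the assumed rates.

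Each option costs a sentence or so and neither needs more patients; (b) also means accepting a less favourable power figure. Only if the sponsor wants both the two-tailed level and 80% power would the target rise to 88 evaluable per group. The choice should be dated before 1-year occlusion is compared between the arms.

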## Discussion

The introduction of minimal invasive endovenous ablation techniques has revolutionized the treatment of saphenous vein insufficiency. Different endothermal techniques have been introduced and tested in many prospective and randomized studies. Although most research is performed in GSVs, limited data on SSV is available. The results of endothermal techniques have proven to be excellent with a long-term anatomical success rate over 90%; therefore, the aim for future studies, especially in SSV, is diminishing heat-related complications, for example, pain and nerve injury, without compromising anatomical and clinical success. Until now the gold standard for the treatment of SSV insufficiency remains unclear.

This trial is designed to compare the anatomical success at 1 year after MOCA™ with RFA.

A secondary aim is to investigate whether MOCA™ is associated with a significant reduction in post-procedural pain. A major point of discussion is the choice for RFA above EVLA techniques. Although the meta-analysis of Van de Bos *et al*. showed the superiority of endothermal ablation (EVLA) in terms of anatomical success at 1 to 5 years follow-up [10], the more recent RCT of Rasmussen *et al*. has proven that the results of RFA using the ClosureFast device are at least similar to EVLT. In this randomized trial, RFA was associated with significantly less post-procedural pain compared to EVLA [24]. Furthermore, an important consideration in choosing ClosureFast is the uniformity of this technique, while in the case of ELVA, discussion about different tip designs and wavelengths might occur.

It has been proven that minimally invasive techniques will lead to a lower incidence of nerve injury in the SSV compared to conventional surgery (11% versus 28%). However, sural nerve injury is still considered a major and potentially underreported complication [25, 26]. Due to the fact that no heat and tumescent is used in MOCA™, nerve injury after SSV ablation might become a redundant complication.

In conclusion, the MESSI trial is a multicenter randomized controlled trial that aims to show a similar anatomical success of MOCA compared to RFA. Additionally, we hypothesize that this is accompanied by comparable clinical success and a reduction in post-procedural pain after MOCA™ compared with RFA.

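### The 80% power at 74 per group holds for true rates of 97% (MOCA) and 88% (RFA), not for no difference; with both arms at 88% it is about 10%

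*Protocol article*

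**What the plan says.** The Sample size calculation section frames the primary comparison as non-inferiority: "The calculation is based on the hypothesis that MOCA™ will have no inferior occlusion rates at 1 year after treatment compared to RFA". It takes 88% success for RFA from a meta-analysis. For MOCA it says: "Our recent study on MOCA™ in SSV showed an occlusion rate of 97% in the group treated according to our current study protocol". The power statement, for a chi-square test at one-sided 0.05, is that the test "has a power of 80% to observe no difference between both groups, when each group consists of 74 patients"; a 2% range is given in brackets. The evaluable total is 148, raised to 160 for 7.5% loss to follow-up.

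No sentence says that the 80% depends on the gap between 97% and 88%. The closing paragraph of the Discussion says that the trial "aims to show a similar anatomical success of MOCA compared to RFA".

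**The concern.** The power sentence attaches 80% to a scenario of no difference, while the two rates cited just before it differ by 9 points. The two cases are far apart. A non-inferiority test with a 2-point margin has to detect a distance of 9 + 2 = 11 points if MOCA is truly better by 9, but only 2 points if the arms are equal. A size that suits the first case cannot suit the second.

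The stake is what the trial can be expected to show. A reader who takes the sentence at its word, together with the Discussion's aim of similar success, will believe that two equally good treatments would very probably be shown to be so. The design does not have that property.

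**Working it through.** **Inputs** (Sample size calculation): RFA 88%, MOCA 97%, one-sided alpha 0.05 (z = 1.645), power 80% (z = 0.842), 74 per group, loss 7.5%. The 2% range is read as an absolute margin of 2 percentage points; the document gives no other margin.

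**Step 1: reproduce 74.** Farrington-Manning: n = [1.645·√V0 + 0.842·√V1]² / (pM − pR + 0.02)².
- V1 = 0.88×0.12 + 0.97×0.03 = 0.1056 + 0.0291 = 0.1347.
- V0 uses the rates restricted to a 2-point deficit, about 92.9% (RFA) and 90.9% (MOCA): V0 ≈ 0.149.
- n = (0.635 + 0.309)² / 0.11² = 73.6, so 74 per group. Power at 74 is 80.2%.
- 148 / (1 − 0.075) = 160.

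Other variance choices give 69 (unpooled) or 71 (pooled) per group, with 82.5% and 81.5% power at 74. Exact enumeration of the Farrington-Manning test at 97% v 88% gives 84%. Superiority formulas do not fit: 105 per group one-sided, 134 two-sided.

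**Step 2: power at 74 per group for other true rates.** Power = Φ[(pM − pR + 0.02)/SE − 1.645], with SE = √[(pM(1 − pM) + pR(1 − pR))/74].

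| True MOCA | True RFA | Power | Exact score test |
|---|---|---|---|
| 97% | 88% | 82% | 84% |
| 95% | 88% | 63% | |
| 93% | 88% | 43% | |
| 90% | 88% | 19% | |
| 88% | 88% | 10.2% | 10.5% |
| 92.5% | 92.5% | 11.8% | 11.8% |
| 97% | 97% | 17.6% | 13.3% |

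Worked line for 88% in both arms: SE = √(2×0.1056/74) = 0.0534; 0.02/0.0534 − 1.645 = −1.27; Φ(−1.27) = 0.102. With all 80 per group evaluable it is 10.5%.

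**Step 3: the advantage needed.** With RFA fixed at 88%, power reaches 80% at a true MOCA rate of 96.7% (unpooled) to 97% (Farrington-Manning), an advantage of about 9 points.

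**Step 4: precision at equal rates.** The 90% interval half-width with 88% in both arms is 1.645 × 0.0534 = 0.088, or 8.8 points, more than four times the margin. If RFA is observed at 88%, MOCA must be observed about 6 points better for the lower limit to clear −2.

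**Step 5: scale.** For 80% power with both arms at 88%, n = (1.645 + 0.842)² × 0.2112 / 0.02² ≈ 3,265 per group; at 97% in both it is about 900. These figures only show how far apart the two scenarios are.

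**The case against.** The best defence is that nothing is miscalculated. The 74 reproduces, both assumed rates stand directly before the power sentence, and the bracketed words name the non-inferiority principle, so a statistician can recover the calculation. Powering a non-inferiority trial on an expected advantage is legitimate. The hypothesis in the Abstract, Study objectives and Sample size calculation is non-inferiority, which a better MOCA satisfies; only the end of the Discussion speaks of similar success. All of this stands. It shows that the fault lies in the description of the power, not in the number, but it does not make the description true.

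One other combination also gives 74: both arms at 97% with a 7-point margin (n = 73.4). The document states no 7-point margin, and this contradicts the 2% range, so it does not rescue the sentence. Nor does reading no difference as a non-significant result: with equal arms, a 5% test is non-significant about 95% of the time whatever the sample size, so that is not power.

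Some stronger readings are tempting but not supported:
- *That 80% power always needs a 9-point advantage.* That holds with RFA at 88%. At 99% v 93%, 6 points apart, power is about 81%.
- *That the Discussion's figure of over 90% undermines the 88%.* The former is a long-term figure for endothermal techniques as a class; the latter is a 1-year figure for RFA.
- *That 97% was picked merely as the most favourable figure.* The Background does say "Occlusion rates in 50 patients were 100% at 6 weeks follow-up and up to 97% at 1 year", but the Sample size calculation gives a reason: it is the group treated according to the current protocol. The size of that group is not shown.
- *That a null result will be reported as proof of similarity.* No passage says so.

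**Conclusion.** The point holds as a misdescribed power statement. The sample size is correctly computed for 97% v 88%, a 2-point margin and one-sided 0.05. It does not give 80% power when the arms are the same. Under equal true rates between 88% and 97%, power to exclude inferiority of more than 2 points is about 10 to 18%, so the chance of missing the margin is about 82 to 90%. A smaller MOCA advantage over RFA at 88% also leaves power well short of 80%: 63% at a 7-point and 43% at a 5-point advantage.

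This rests on reading the 2% range as an absolute margin and on 74 evaluable patients per group. It does not depend on the variance formula: approximate and exact calculations agree that equal-arm power is far below 80%. A reader might infer that the trial must be enlarged; that does not follow, because a design built on an expected advantage is permissible when the assumption is stated.

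**What to change.** In the Sample size calculation, delete the words claiming power to observe no difference and replace the sentence with something like:

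> *With 74 evaluable patients per arm, power to exclude inferiority of more than 2 percentage points (one-sided 0.05) is about 80% if the true rates are 97% (MOCA) and 88% (RFA); it is about 10% if both are 88%.*

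Align the closing aim in the Discussion with this: similar anatomical success should be concluded only if the lower confidence limit for MOCA minus RFA lies above −2 points.

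The cost is the rewording and a less favourable stated figure. Enrolment, margin, endpoint and procedures stay as they are.
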